### Plans to give access to the full protocol, participant level-data and statistical code {31c}

Upon completion of study procedures and the primary study publications, the full protocol will be uploaded to ClinicalTrials.gov. Data sharing with the broader scientific community will be prioritized as determined by the PI, based on reasonable requests. All data that is published or shared will remain deidentified and participant privacy and confidentiality will be maintained.

## Oversight and monitoring

### Composition of the coordinating center and trial steering committee {5d}

A joint trial steering and data safety monitoring committee (TSC and DSMC) will be made up of an independent chair and two external members not involved in day-to-day conduct of the research trial. The TSC will monitor RCT progress, identify challenges, and facilitate mitigation strategies with the PI.

### Composition of the data monitoring committee, its role and reporting structure {21a}

The DSMC will review adverse events reported by participants, stop the study trial if warranted by data, and advise PI on measures needed to ensure participant safety throughout the trial.

### Adverse event reporting and harms {22}

Adverse events will be collected during monthly phone calls to participants during the 26-week intervention. In case of a serious adverse event during the study, participants will be instructed to call 911 or report to the nearest emergency room. The TSC/DSMC will review all adverse events every 3 months and classify them based on the definitions from the January 2007 OHRP *Guidance on Reviewing and Reporting Unanticipated Problems involving Risks to Subject or Others and Adverse Events, OHRP Guidance*. The TSC/DSMC will stop the study or advise on modifications to the protocol to maintain safety as warranted by the data.

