### Objectives {7}

The primary aim of the SuPA Mobility Trial is to assess if a 26-week HC intervention that aims to increase time spent in moderate to vigorous PA (MVPA) by at least 50 min per week can improve mobility, as measured by the SPPB, versus a 26-week health education (ED) program in older adults with mobility limitations. Our secondary objectives are to evaluate the effects of HC compared with ED in the following outcomes: (i) time spent in MVPA and average daily awake sedentary time, (ii) 4-m walk gait speed, (iii) the capacity to complete a 400-m walk in ≤ 15 min (yes/no), (iv) cognitive function, (v) community mobility, (vi) fatigue, (vii) muscle strength, (viii) mood, (ix) quality of life, and (x) sleep. We will also perform a 26-week follow-up assessment to determine whether the benefits of HC versus ED persist 6 months after cessation of the intervention. Additionally, we will perform a concurrent economic evaluation to determine whether HC compared with ED is cost-effective at intervention cessation and follow-up.

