### Relevant concomitant care permitted or prohibited during the trial {11d}

All participants will seek health care as usual, without any care being prohibited throughout trial. Health care utilization will be assessed via monthly self-report diaries and questionnaires assessed every 3 months throughout the trial duration.

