#### Falls

Falls will be prospectively documented by all participants on a monthly basis via calendars provided by the research team. Participants will be asked to report any falls directly to the research team after they occur. We will complete a follow-up falls interview over the phone to obtain information regarding the fall and determine if any adjustments to the study protocol and interventions are required.

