#### Health resource utilization (HRU)

Cost data will be collected monthly via HRU diaries, and these self-report cost diaries will be confirmed during in person assessments or via telephone calls every 3 months using the HRU questionnaire [53], which is based on validated cost questionnaires [54–56]. The HRU questionnaire is utilized to collect specific details on (1) health professional visits; (2) hospital, rehabilitation facility, and inpatient clinic visits; (3) laboratory procedures or investigations; and (4) medications. Using a fully allocated hospital cost model (for in-patient costs) and the British Columbia provincial guide to medical fees (for outpatient costs), we will assign health care resource utilization on a per participant basis. Evidence from a systematic review of 15 studies demonstrates good agreement between self-reported questionnaires on resources utilization and administrative data [57].

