### Participant timeline {13}

Participant enrolment began July 2023 and the first participant was randomized September 5, 2023. We expect participant recruitment, assessments, and follow-up visits to be completed by October 2026. Participants will undergo a phone screening to determine preliminary eligibility. If appropriate, participants will be invited for an in-person screening. Within 1 month of the in-person screening, participants will complete the remainder of the baseline assessments and will be randomized to either the HC or ED group. Participants will partake in intervention procedures for 26 weeks. Upon completing the intervention, participants will be followed for another 26 weeks. Upon the final follow-up assessment at 52 weeks, participants in the ED group will receive an initial HC visit followed by 2 additional HC calls and receive access to exercise-related materials. The participant timeline of assessments is shown in Table 2.

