**Table 2 Tab2:**
[figure not shown]
Participant timeline of assessments

*Falls data will be collected monthly throughout the trial

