### Plans to promote participant retention and complete follow-up {18b}

Participants in the HC group will have regular communication from bi-monthly to monthly sessions with their BAP coach to promote retention and adherence to the intervention. Participants in the ED group will have the same structure of engagement with group education sessions to promote retention and adherence. Education session attendance will be incentivized by entering participants into a gift card drawing every other session. Throughout the study intervention and follow-up time frame, participants will receive monthly communication from study personnel to assess falls and other outcomes. In a previous study utilizing a similar HC protocol in adults with mild cognitive impairment, adherence rates to PA recommendations with ≥ 73% and attrition rates were ≤ 10.4% [59, 60].

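### Systematic adverse-event collection is tied to the 26-week intervention, while benefit, monthly contact and safety oversight run to week 52; adverse events other than falls have no stated collection route in weeks 27-52

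*Protocol article*

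**What the plan says.** The harms section of the protocol article (Adverse event reporting and harms {22}) sets a route and a period: "Adverse events will be collected during monthly phone calls to participants during the 26-week intervention". It then has the joint steering and safety committee review all adverse events every 3 months.

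Other sections run longer:

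- **Participant timeline {13}:** "Upon completing the intervention, participants will be followed for another 26 weeks".
- **Objectives {7}:** the later assessment is there to "determine whether the benefits of HC versus ED persist 6 months after cessation of the intervention".
- **Plans to promote participant retention {18b}:** "Throughout the study intervention and follow-up time frame, participants will receive monthly communication from study personnel to assess falls and other outcomes".
- **Composition of the data monitoring committee {21a}:** the committee advises on participant safety for the whole trial.

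Two kinds of harm-related data are explicitly collected to the end. On falls, the Falls section says "Falls will be prospectively documented by all participants on a monthly basis via calendars provided by the research team", and the Table 2 footnote says "Falls data will be collected monthly throughout the trial". On care received, the section on concomitant care {11d} says "Health care utilization will be assessed via monthly self-report diaries and questionnaires assessed every 3 months throughout the trial duration", and the questionnaire asks among other things about "hospital, rehabilitation facility, and inpatient clinic visits".

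**The concern.** The coaching is meant to establish self-directed activity that outlasts the coaching, and the 52-week visit tests whether its effect does so. If activity persists, so may its harms, for example musculoskeletal or cardiovascular events. Participants are aged 70-89, have mobility limitations and reported almost no moderate to vigorous activity at entry. After week 26 the coaching arm has no scheduled coach contact, and that is also when the stated adverse-event calls end.

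Two things are at stake. First, the 52-week results would carry less complete safety information than the 26-week results. Second, a committee with a whole-trial remit would, by the stated route, receive no general adverse events from participants past week 26. Some of those participants reach that stage while others are still being coached, so the information could be of use during the trial.

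The control arm is offered coaching only after the 52-week assessment (Strategies to improve adherence {11c}). A randomised comparison of harms is therefore available up to that point if the data are collected.

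**Working it through.** The plan gives no figure on this point to reproduce. The check compares collection windows and sizes the part of follow-up outside them.

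**Inputs**

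- Adverse-event window: 26 weeks (harms section {22}).
- Total follow-up: 26 + 26 = 52 weeks (Participant timeline {13}).
- Participants: 290, with 15% dropout allowed for (Sample size {14}).
- First randomisation 5 September 2023; visits complete by October 2026 (Participant timeline {13}).

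**Windows side by side**

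| Item | Stated period | Share of 52 weeks outside it |
|---|---|---|
| General adverse events, monthly calls | weeks 0-26 | (52 - 26)/52 = 50% |
| Falls, monthly calendars, all participants | whole trial | 0% |
| Health-care use, monthly diaries and 3-monthly questionnaires | whole trial | 0% |
| Monthly contact by study personnel | intervention and follow-up | 0% |
| Safety committee remit | whole trial | 0% |

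**Person-time outside the adverse-event window**

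- Upper bound: 290 x 26/52 = 145 person-years.
- If all of the 15% dropout occurs before week 26: 145 x 0.85 = 123 person-years.

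These figures are the time in which adverse events other than falls have no stated collection route. They are not time without any safety-relevant data.

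**Overlap with ongoing coaching**

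Assume that coaching starts at randomisation. The first participant then passes week 26 in about March 2024. With last visits in October 2026 and 52 weeks of follow-up, randomisation could run to about October 2025 and coaching to about April 2026. Events in early participants after week 26 could thus inform the committee for up to about two years while later participants are still in the intervention.

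**What the other data can and cannot supply**

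- Falls are covered, with a telephone interview after each fall.
- Health-care-use records would show events that led to care. They are described as cost data, and no section sends them to the committee or has them classified as adverse events. Events for which no care was sought, such as some musculoskeletal pain, would not appear in them.
- Fatigue, mood, sleep and quality of life (which has a pain item) are measured at 39 and 52 weeks. They are scale scores at fixed times, not event reports.

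**The case against.** The strongest reply is that the harms section names one route and does not say that later events go unrecorded. The same section refers to serious events during the study and to review of all adverse events, and the monthly contacts in follow-up cover falls and unspecified other outcomes. Asking actively about adverse events while an intervention is being delivered is also a defensible choice in a study that the article calls minimal risk, where participants limit their own activity. Finally, the document is a condensed article, and the full protocol may say more.

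Part of this stands. A reader might infer that no harms at all are recorded or compared after week 26, so that up to 145 person-years are without safety ascertainment. The documents do not support that: falls and health-care use are collected in both arms to week 52, and the Discussion lists falls among the outcomes on which the effect of coaching will be evaluated. A reader might also infer that the trial claims a year of benefit against half a year of harm. It does not: persistence at 52 weeks is a question to be tested, and the primary aim concerns the 26-week intervention, which the adverse-event calls cover in full. Nor does anything suggest that the two arms are asked differently.

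The rest does not remove the point. The reference to serious events during the study tells participants where to seek help and sets no collection procedure. The unspecified outcomes in the monthly contacts could include adverse events, but the text does not say so, and the section that governs harms gives the narrower period. This is a stated window, not a detail left out by condensation. If collection to week 52 is already intended, the sentence is misworded and still needs correcting.

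**Conclusion.** The point holds in a limited form. As written, systematic collection of adverse events covers 26 of 52 weeks, while assessment of persisting benefit, monthly contact and safety oversight cover all 52. The shortfall is half of planned follow-up, 123 to 145 person-years under the protocol's own enrolment and dropout figures. It applies to adverse events other than falls, and bites hardest on those that do not lead to use of health care. Events that do lead to care are recorded, but with no stated path to the committee and no stated classification as adverse events.

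The conclusion assumes that the harms section means what it says and that the monthly contacts in weeks 27-52 include no general adverse-event question. The primary analysis is unaffected. This is a worthwhile, low-cost improvement to the safety data, not a flaw that undermines the trial.

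**What to change.** Amend the harms section {22} so that adverse events are asked about in both arms at the existing monthly contacts through week 52, sent to the joint steering and safety committee for its 3-monthly review, and reported by arm for weeks 0-26 and weeks 0-52. This brings the section into line with the retention section {18b} and the committee's remit {21a}.

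The cost is a short amendment, a few more questions in contacts that already take place, and a little more data entry and committee review. Treatment and visit schedule do not change. For participants already past week 26, events not asked about at the time may not be fully recoverable, so an early amendment is worth more than a late one.

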### Frequency and plans for auditing trial conduct {23}

The joint TSC and DSMC will meet every 3 months to review safety data and monitor RCT progress. As this is a minimal risk study, the University of British Columbia Research Ethics Board will review trial conduct on an annual basis.

### Plans for communicating important protocol amendments to relevant parties (e.g., trial participants, ethical committees) {25}

Any protocol amendments recommended by the TSC/DSMC and approved by the research ethics board that impact study participants will be discussed with individuals in the trial as part of maintaining continual active informed consent. Approved protocol amendments will be updated on ClinicalTrials.gov.

### Dissemination plans {31a}

The results of this study will be utilized to make evidence-based recommendations to promote PA in older adults to promote mobility and prevent disability. We plan to disseminate our results widely through targeting our dissemination efforts to 3 primary groups: (1) older adults and community stakeholders, (2) clinicians and health practitioners, (3) and researchers.

Through our established relationships within the community, we will host public talks to share our findings with stakeholders. We plan to organize a 2-day scientific symposium in collaboration with the Centre for Aging Smart and Vancouver Coastal Health Research Institute to exchange updates on mobility in aging with leaders in the scientific community. A companion forum will be held in a similar fashion to disseminate results to the lay public and broader community health professionals. Study results will be shared broadly through conference presentations and peer-reviewed publications as well as through an established network, Physical Activity for Precision Health [65], a network of Canadian and international researchers, which includes a Patient Advisory Group.

## Discussion

Previous research has demonstrated the importance of MVPA on improving mobility and reducing MMD risk in older adults with mobility limitations. However, there is a need to identify strategies that can be delivered at scale for this population. The proposed research will utilize a novel HC intervention to promote MVPA by a minimum effective dose in older adults with mobility limitations. The findings of this study will provide insights on the effect of a HC intervention on mobility in older adults with mobility limitations and thus, at risk for MMD. This study will evaluate effects of HC on secondary health outcomes, including PA levels, gait speed, 400-m walk, cognitive function, fatigue, strength, functional and community mobility, mood, quality of life, sleep, and falls. Finally, this study will provide an estimate of the cost-effectiveness of the HC intervention. These findings have the potential to reduce the personal and societal burden of limited mobility and MMD via a strategy that can be widely implemented.

### Trial status

This protocol was originally approved May 1, 2023 (Version 3). The first participant was randomized September 5, 2023, and study-related visits are expected to be completed by October 2026.

## Data Availability

The final data set will remain within the study team under the primary responsibility of the primary investigator, who will determine sharing of the data set upon reasonable request.

## Abbreviations

ED: Health education program
HC: Health coaching
MMD: Major mobility disability
MVPA: Moderate to vigorous physical activity
PA: Physical activity
SPPB: Short Physical Performance Battery
